## Abstract

**Background:**

Adolescents with cerebral palsy (CP) show a reduced physical activity (PA). Currently there are no interventions for adolescents with CP in this critical life phase that optimise and maintain the individuals' physical activity in the long term. To develop such a program it is important to fully understand the factors that influence physical activity behaviours in adolescents with CP. The aim of this study is to explore what makes it easy or hard for adolescents with CP to be and to become physically active.

**Methods/Design:**

A qualitative research method is chosen to allow adolescents to voice their own opinion. Because we will investigate the lived experiences this study has a phenomenological approach. Thirty ambulatory and non-ambulatory adolescents (aged 10-18 years) with CP, classified as level I to IV on the Gross Motor Function Classification System and 30 parents of adolescents with CP will be invited to participate in one of the 6 focus groups or an individual interview. Therapists from all Children's Treatment Centres in Ontario, Canada, will be asked to fill in a survey. Focus groups will be audio- and videotaped and will approximately take 1.5 hours. The focus groups will be conducted by a facilitator and an assistant. In preparation of the focus groups, participants will fill in a demographic form with additional questions on physical activity. The information gathered from these questions and recent research on barriers and facilitators to physical activity will be used as a starting point for the content of the focus groups. Recordings of the focus groups will be transcribed and a content analysis approach will be used to code the transcripts. A preliminary summary of the coded data will be shared with the participants before themes will be refined.

**Discussion:**

This study will help us gain insight and understanding of the participants' experiences and perspectives in PA, which can be of great importance when planning programs aimed at helping them to stay or to become physically active.

## Background

Cerebral Palsy (CP), with a prevalence of 2-3 per 1000 children, is the most common motor disability in paediatric rehabilitation [1]. Because of their motor problems, children and adolescents with CP experience participation restrictions and limitations in physical activities [2,3]. Based on Lelieveld et al. we define physical activities (PA) as all body movements resulting in an increased energy output from the resting position [4]. Children and adolescents with CP show lower levels of PA compared to their healthy peers [5,6]. Lower levels of PA contribute to a reduced physical fitness [5,7], which may increase the risk of developing secondary health problems such as pain and fatigue [8], cardiovascular disease and diabetes mellitus later in life [9]. Moreover, PA is assumed to have a positive relation with health related quality of life and psychosocial functioning [10].

Participation in PA is influenced by age and gross motor function in adolescents with CP. With increasing age, adolescents with CP show a decrease in PA [6,11,12]. Moreover, adolescents with more severe motor problems are participating less in PA than adolescents with less severe motor problems [11,12]. Recent reviews that have evaluated exercise programs in children with CP suggest improvement in muscle strength, coordination and aerobic fitness [13,14]. However, these effects were only partially maintained at follow-up [14] and there is little evidence that these effects carryover into PA and participation [13,14]. Currently there are limited studies to support that current interventions optimise and maintain the individual's PA in the long term [15,16]. We are far from the implementation of promoting PA and changing PA behaviour in practice.

In adolescence, young people develop their adult lifestyle. Health promotion in this developmental phase is critical for all people. Therefore, especially in adolescents with CP, participation in PA should be promoted. Unfortunately, adolescents with CP have to face a discontinuity of care at this stage, as paediatric rehabilitation will end [17]. Current insights suggest that new interventions with a focus on physical fitness and an active lifestyle are important to improve and maintain health in adolescents with CP [18]. The age-specific interventions should primarily address the change in behaviour of adolescents with CP themselves, since from this age adolescents become gradually more autonomous from their parents and develop their personal lifestyle. To develop such an intervention it is important to fully understand the factors that influence PA behaviour in adolescents with CP and factors that make them willing to participate in such programs.

Several studies have been done to investigate barriers to and facilitators of PA in persons with disabilities. In these studies a range of physical, psychological and environmental factors that facilitate or constrain people with disabilities from PA, has been identified [19-22]. Although in one study barriers of and facilitators to PA in adults with CP have been explored [19], no studies have been done to investigate if the same barriers and facilitators exist for adolescents with CP [who are in phases of developing their adult lifestyle]. The present study will build on ongoing research from [name] in the Netherlands, exploring barriers and facilitators of PA in ambulatory children and adolescents with CP, classified at level I and II on the Gross Motor Function Classification System (GMFCS). In the present study we will not only look at the barriers and facilitators, but also at solutions for these barriers. Moreover we will look at ambulatory and non-ambulatory adolescents (10-18 years) classified at level I to IV on the GMFCS in the province of Ontario, Canada.

We aim to develop and evaluate a program to teach people how to promote PA and encourage an active lifestyle in adolescents with CP who are learning to care for themselves; the Stay-FIT study. The present pilot study is a part of the Stay-FIT study. To find out what would be the most optimal Stay-FIT intervention, we need to know more about what issues arise for adolescents with CP, concerning PA. In other words, we need to understand their perspective. Only recently a questionnaire was developed, which focuses on adolescents' opinion about health services, where usually the focus is on adults' or parents' perceptions [23]. Adolescents greatly value their right to make their own decisions and advocate for themselves. Therefore, their views and opinions should be a pivotal starting point in the planning of every program geared towards their health and wellbeing [24]. Nevertheless, most adolescents are still living at home with their family, which makes the role of their parents or caregivers still important. Also the view of therapists in Children's Treatment Centres can be of great value, as they continue to monitor or treat children with CP into their adolescence. The research question of this study is: "What makes it easy or hard for adolescents (age10-18 years), with CP (with a broad range of severity in motor problems) to be and to become physically active?" The main objective is to explore the experience and perspectives of adolescents with CP and their parents. A secondary objective of this study is to survey therapists on facilitators and barriers to physical activity of their clients by using a questionnaire.

## Methods/Design

We explored different methods to find out which method best addressed our research question. Firstly, we considered both quantitative and qualitative approaches. Secondly, different types of qualitative research and qualitative data collection methods were thought over.

### Qualitative versus quantitative research

Quantitative research has the aim to test well-specified hypotheses concerning some predetermined variables [25]. However, before this can be done, these hypotheses need to be generated based on knowledge and theory of the specified topic. We found only two published articles on studies in which barriers to PA in adults with disabilities were investigated using a standardized survey [26,27]. Based on these articles and after contacting the first author of these articles ([name], personal communication November 2009), we concluded that no such quantitative measures exist for adolescents with CP.

When little is known about a certain topic qualitative research can offer insight into social, emotional, and experiential phenomena in health care and tend not to answer "whether" or "how much" but rather to explore "what", "how", and "why" [25]. Another advantage of qualitative research is that complex phenomena or areas not accessible to quantitative research can be explored [28]. Qualitative research methods allow people to voice their own opinion, rather than conforming to categories and terms imposed on them by others [29].

We concluded that a qualitative approach can be of great use to allow adolescents to voice their opinion, considering we eventually want to develop a PA program for adolescents of different ages, with different preferences and needs. This decision seems appropriate considering the fact that little is known about PA related barriers and facilitators in adolescents with CP and no suitable quantitative measures exist to investigate this concept.

### Types of qualitative research

Qualitative research types are based on different traditions of inquiry and we looked for the best fit between our research question and a specific type. Different research types were explored, such as: a biography, a phenomenology, a grounded theory, ethnography and a case study [30]. A phenomenology can be used for describing the meaning of the lived experiences for several individuals about a concept or phenomenon and seemed most appropriate for our study. Other types that were considered but not chosen were: a grounded theory study with the intent to generate or discover a theory and an ethnography which is a description of and interpretation of a cultural or social group or system.

In conclusion, because the aim of the present study is to investigate the lived experiences of adolescents in PA participation, we will use the phenomenological qualitative approach following the interpretive school, acknowledging presuppositions on PA in adolescents. To our knowledge, no data has been published about adolescents' lived experiences of PA in this manner.

### Data collection methods

The most common types of qualitative data collection methods are field observation (direct observation or indirect observation), interviews (semi-structured, in-depth, individual interviews and focus groups), and document analysis (such as charts, journals and correspondence) [25]. These methods can be used separately or in combination.

To us focus groups make the most sense for data collection for both the exploratory character of the study (What makes it easy or hard for adolescents with CP to be and to become physically active) and the study population (ambulatory and non-ambulatory youth with CP in an age range 10 to 18 years, and parents of adolescents with CP). We will combine the focus groups with additional individual interviews with youth or parents who can contribute in optimizing maximal variation in experiences and perspectives. In summary, we choose a method that would help us to get more a breadth rather than depth in the Stay-FIT pilot study.

Focus groups are semi-structured group meetings, which intend to gather information on a certain topic based on the participants' interaction [31]. Focus groups are unique because they allow the investigator to collect data both from the individual and the individual as part of a larger group [32]. The interaction of group members produces something that is not reducible to individual members or group opinions [32]. They are helpful in understanding how stakeholders regard specific experiences or incidents, fill in gaps in meaning and help understand the 'why' behind attitudes and behaviours [32].

To evaluate therapists' opinions on facilitators and barriers to physical activity of their clients, a questionnaire will be constructed specifically for this purpose. The survey is based on the results of a recent study in the Netherlands on perceived barriers to and facilitators of physical activity in young adults with childhood-onset disabilities [19], expert opinion of the study group members, and feedback from group discussions with physical therapists and occupational therapists from the local Children's Treatment Centre (CTC) "Children's Developmental Rehabilitation Programme (CDRP)" at McMaster Children's Hospital, Hamilton, Ontario, Canada. Therapists of CTC's in the province of Ontario will be invited to complete an online survey.

### Sample selection and recruitment

Adolescents, parents and therapists will be recruited from six Children's Treatment Centres (CTC's) in Ontario who expressed their interest in participating in the Stay-FIT Study and their community network. These centres vary in terms of geography (urban/rural), caseload size, and regional policy planning region.

Adolescents with CP (aged 10-18 years), classified at level I, II, III or IV on the Expanded and Revised-Gross Motor Function Classification System (GMFCS-E&R) [33] will be invited to participate in one of the focus groups or alternatively an individual interview. On behalf of the research team a Site Coordinator in each centre will send out Stay-FIT pilot study informational flyers to adolescents with CP and their parents. Coordinators are instructed to recruit with 'purposeful sampling' strategy in order to include adolescents in different age range and GMFCS level. To maximize the experiences and perspectives coordinators will be encouraged to include both typical and unusual cases with regards to the adolescents' physical activity patterns. These can be, for instance adolescents that are known to be very active or not active at all.

Through the same six CTC's parents of adolescents with CP (aged 10-18 years) will be invited to participate in the study and join one of the focus groups or alternatively an individual interview. To increase variety, we will also include parents of adolescents who are not participating in the Stay-Fit study.

Physical therapists, occupational therapists and recreational therapists from all 20 CTC's in Ontario (see http://www.oacrs.com) with a range of size (large and small) and setting (rural versus urban) will be asked to fill in the survey.

### Sample size

To reach saturation on a certain topic, a minimum of 4 to 5 focus groups is required [31]. With six CTC's participating, we plan to conduct six focus groups in the present study. Saturation will be checked after each meeting. We aim for six to eight participants per focus group as the optimal number. If there are fewer than 5 participants, the dynamics and the interaction of the group will be limited. If there are more than 10 participants there will not be enough time to let every participant express their view [31]. To assure this optimal number of participants we will recruit 12 to 15 participants per focus group. Overall we aim for 30 adolescent participants and 30 parent participants at a minimum. A response rate of 30% of therapists in the CTC's is anticipated based on previous work of our study group.

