	**Environmental factors** • Social support: - Anyone to exercise with (friends/family) - Anyone encouraged you to be active - Anyone told you exercise is important for you • Physical support - Your parents or other people are able to drive you to activities - Transportation is available - Staff able to get the help you need to participate e.g. get changed, use equipment - Are you afraid of hurting yourself • Attitudes - Teasing or bullying - Staring - Embarrassed about how you look or move	**Environmental factors** • Physical support - Transportation and convenience of location and getting to and from activity - Physical support of a family member or program staff - Knowledgeable staff - Perceived safety • Social support - Attitudes of other children/adults - Acceptance - Financial support/subsidized costs • Access to information about available activities/personal guidance for a training plan
		
**Closure**	"Given the discussion on facilitators and barriers, we would like to know what your ideas are for the 'best' Stay-FIT intervention for youth." (Structure, timing, content, setting/location, and people involved, etc.)	

1. What are you doing to be physically active and what helps you to stay physically active?

2. What is keeping you from doing the activities you want to do?

3. What could be a solution for the things that keep you from being physically active?

On the flip-chart the different themes identified from the demographic forms will be showed. There will be one column addressing the things that make it hard to be physically active and one column addressing the things that are helping to be physically active. During the focus group new ideas can be added and solutions can be discussed. In order to build on previous research on barriers to and facilitators of PA, we identified 4 themes for both the focus group with adolescents and the focus group with parents (Table 1). These themes were selected based on previous studies [19-22] and experts experience with adolescents with CP to assure the fit with the adolescent population. At the end of the discussion, these themes will be addressed when they are not mentioned before by the participants.

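### As written, six focus groups in total fit neither a 4-to-5-group saturation minimum for two separately grouped populations nor the 30 + 30 participant target

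*Protocol article*

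**What the plan says.** The Sample size section gives a benchmark: "To reach saturation on a certain topic, a minimum of 4 to 5 focus groups is required [31". The planned number follows directly: "With six CTC's participating, we plan to conduct six focus groups in the present study". Saturation is to be checked after each meeting, without saying for which population.

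The same section sets the group size, "We aim for six to eight participants per focus group as the optimal number", treats fewer than 5 as too few for interaction and more than 10 as too many for the time available, and sets the overall target: "Overall we aim for 30 adolescent participants and 30 parent participants at a minimum".

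The Abstract (Methods/Design) says that 30 adolescents and 30 parents "will be invited to participate in one of the 6 focus groups or an individual interview". Six is therefore presented there as the number for both populations together.

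The section on focus group content treats the two populations as meeting separately, with "4 themes for both the focus group with adolescents and the focus group with parents". Table 1 has one column of prompts for each. Adolescents are prompted on, for example, bullying, staring and embarrassment; parents on family preferences, time commitment and subsidised costs.

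Both populations are in the main objective, stated at the end of the Background: "The main objective is to explore the experience and perspectives of adolescents with CP and their parents".

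**The concern.** The benchmark of 4 to 5 groups is the only reason the article gives for thinking that its number of groups is enough. It is set against a total of six, but those six are shared by two populations that do not sit in the same room and do not discuss the same list of prompts. A total that exceeds the benchmark does not show that either population reaches it.

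The study is built on hearing adolescents in their own words, and its results are meant to shape the Stay-FIT intervention. If saturation is judged over all meetings together, parents repeating familiar themes could make the material look complete while adolescents are still raising new ones. The article does not say that the check will be pooled, but nothing in it prevents that. A reader of the results could not tell whether saturation was reached among adolescents, among parents, or only in the combined material.

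**Working it through.** **Inputs**
- Minimum for saturation: 4 to 5 groups (Sample size).
- Planned groups: 6 in the study (Sample size; Abstract).
- Populations meeting separately: 2 (Content focus groups Stay-FIT pilot; Table 1).
- Preferred group size: 6 to 8; limits 5 and 10 (Sample size).
- Target: 30 + 30 = 60 at a minimum (Sample size).

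**1. The plan's own figure.** 6 centres × 1 group = 6. Set against 4 to 5, six is enough if all groups count towards one total.

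**2. The benchmark applied to each population.** Groups needed = 2 × 4 = 8 to 2 × 5 = 10. Planned: 6.

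**3. Every division of six.** The split is not stated, so all are listed (order of the populations immaterial):

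| Split | Larger share | Smaller share | Both at least 4? |
|---|---|---|---|
| 3 + 3 | 3 | 3 | No |
| 4 + 2 | 4 | 2 | No |
| 5 + 1 | 5 | 1 | No |
| 6 + 0 | 6 | 0 | No |

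The smaller share is at most 6 / 2 = 3, which is below 4. The result does not depend on which split was intended.

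**4. Capacity.** 6 groups × 6 = 36 and 6 × 8 = 48, against a target of 60. The remainder is 60 − 48 = 12 to 60 − 36 = 24 people, who would have to be interviewed individually. The article calls the interviews additional and gives no number for them. Placing everyone in groups gives 60 / 6 = 10 per group, above the preferred size and exactly at the upper limit.

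**5. Readings under which the minimum is met.**
- *Pooled:* all six groups count towards one topic, and 6 is at least 5. The benchmark is met, but saturation is then not shown for either population alone, and the capacity gap in step 4 remains.
- *Six per population:* 2 × 6 = 12 groups. At the lower limit of 5, 6 × 5 = 30, which matches each target exactly; at the preferred size, each population has 6 × 6 = 36 to 6 × 8 = 48. These figures are coherent, but the stated number of groups would then be half the true one.

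**The case against.** The strongest reply is that one adolescent group and one parent group were meant at each of the six centres. The two populations are recruited separately through the same centres, and six groups of 5 give exactly the 30 stated as a minimum for each. On that reading the benchmark is met in both. This stands as a possible intention, but not as what is written: the Sample size section and the Abstract both say six, and neither says twelve or six per population. If twelve was meant, the stated number is wrong and still needs correcting.

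A second reply is that the benchmark is stated per topic, not per population, and that there is one research question, one definition of physical activity and one closing question. This also has some force. Whether the cited source intends the figure per population cannot be settled from the article. Against it, the groups are separate, the prompts differ, and both populations are named in the main objective.

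A third is that individual interviews and a check after each meeting fill the gap. They help, but the benchmark is expressed in focus groups, the interviews are planned to widen variation, and no rule for adding groups is given.

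A fourth is that a journal article leaves such detail to the full protocol. That would excuse a missing allocation table. It does not excuse stated figures that do not fit together.

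A reader might infer that each population gets three groups, a shortfall of (4 − 3)/4 = 25% to (5 − 3)/5 = 40% in each. The article does not support this: the even split is suggested only by the equal targets and is stated nowhere.

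**Conclusion.** The point holds as an inconsistency between stated figures. With six groups in total and separate meetings for adolescents and parents, at least one population has fewer than four groups under any split; 8 to 10 would be needed for both to reach the stated minimum. Six groups of the preferred size also leave 12 to 24 of the 60 targeted participants outside the groups.

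This rests on two assumptions: that six is the study total, as both statements say, and that the benchmark is meant to support saturation in each population, which the separate groups and the main objective suggest but the article does not spell out. If saturation is pooled, or if twelve groups were intended, the benchmark is met; the text then needs to say so.

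It would go too far to conclude that saturation will not be reached, or that the check is pooled. The article establishes neither. What can be said is that the stated number of groups does not support a claim of saturation in both populations.

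**What to change.** In the Abstract and in the Sample size section, state the number of focus groups for adolescents and for parents, and reconcile these with the group size of 6 to 8 and the 30 + 30 target. Check and report saturation separately for each population.

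If six is the total, do not present the 4-to-5 minimum as supporting saturation in each population, and state how many adolescents and how many parents will be interviewed individually. If six per population was meant, write twelve in both places.

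The cost is a less favourable saturation statement and slightly more analysis work. Running more groups is optional and not free. Four groups per population would average 30 / 4 = 7.5 people and five would average 30 / 5 = 6, both within the preferred size. But the plan recruits 12 to 15 people per group, so 8 to 10 groups mean recruiting 8 × 12 = 96 to 10 × 15 = 150 people, against 6 × 12 = 72 to 6 × 15 = 90 for six. Neither eight nor ten groups divides evenly over six host centres, and placing all 30 of a population in groups leaves nobody for the planned interviews unless more are enrolled.
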